### Statistical analyses

All analyses will be carried out according to the intention-to-treat principle.

Compliance rates between groups will be compared by means of a multivariate linear regression analysis using compliance as a continuous dependent variable. Cox-regression analysis will be used to compare ankle recurrence risk between the intervention and the control group. Absence from sports will be compared between the two groups using a Mann–Whitney test, since absence from sports due to an injury is not normally distributed. For all analyses, variables will be checked for confounding and/or effect-modification and will be adjusted for accordingly.

Mean direct, mean indirect and total costs will be estimated and compared between the two groups, both for the costs per athlete in the injured population and for the costs per athlete in the total population. Because costs will not be normally distributed, 95% confidence intervals for the differences in mean costs will be obtained by bias-corrected and accelerated bootstrapping with 2000 replications. Differences in costs and differences in ankle sprain recurrences will be included in a cost-effectiveness ratio, which estimates the incremental costs to prevent one ankle sprain recurrence. Confidence intervals for the cost-effectiveness ratio will be calculated with bootstrapping, using the bias-corrected percentile method with 5000 replications. Uncertainty of this ratio will be evaluated by presenting a cost-effectiveness plane and sensitivity analyses will be performed to check the robustness of the results. An acceptability curve will also be presented.

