### Study outline

#### ***Randomisation procedure***

After athletes have finished ankle sprain treatment by means of usual care, they will be randomised to one of the two study groups with stratification for initial treatment (i.e. medical or non-medical). Randomisation will take place at the end of treatment. This will minimise the risk of allocation bias. In addition, this will provide room to contact the medical care provider(s) involved in the athletes’ treatment. Medical care providers will be informed about the study in which the athlete partakes and will be asked to follow their usual treatment and/or rehabilitation program. Furthermore, they will be asked to encourage the athlete to take up their allocated intervention program after treatment and/or rehabilitation has ceased.

Athletes allocated to the ‘regular’ intervention group will receive a standardized eight-week proprioceptive training program, consisting of a balance board (machU/ MSG Europe BVBA), and an instructional booklet. This program has been shown to be effective in reducing recurrence injury risk in previous randomized controlled studies [9,10].

Athletes allocated to the ‘App’ group will also receive a balance board (machU/ MSG Europe BVBA), but the standardized eight-week proprioceptive training program will be provided through an interactive smartphone application, which is freely available for Android and iOS users. These two platforms are the most commonly used operating systems on smartphones (of all smartphones 79.3% runs on android, 13.2% on iOS) [13]. Thereby, selection bias is considered minimal. All athletes receive the same balance board. Both the instruction booklet and the ‘Strengthen your ankle’ App contain the same training program and six basic exercises (Figure 2).

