### Baseline measurement

The online baseline questionnaire gathers information of each athlete on demographic variables, physical characteristics, sports & injury history, use of preventive measures, knowledge on injury prevention, severity of the current ankle sprain and subsequent treatment and/or rehabilitation.

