### Compliance

Compliance (primary outcome) measurements will commence after randomisation (i.e. after treatment and at the start of the allocated intervention), and will take place weekly for the duration of the program (8 weeks). These measurements will gather information for each athlete on the number and sets of executed exercises. In addition, online questions will be asked regarding the clarity of the instructions provided, difficulty of the exercises and recurrence of an ankle sprain.

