### Sample size

Sample size calculations are based upon the primary outcome measure compliance, and are based upon previously established compliance rates to the same program when advocated through written materials [12]. Full compliance rates in the written materials’ group are expected to be around 25%. A doubling of this rate to at least 50% is considered to be clinically relevant. Based upon a beta of 0.90 and an alpha of 0.05 a total of 158 athletes is required divided across both study groups. In our experience from previous comparable studies the dropout rate during a 12 months follow-up is about 20%. This would mean that a sample of 190 athletes is needed per group.

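### Covariates and effect-modifiers for the randomised comparisons, including the primary one, are to be chosen by checking the trial data instead of being fixed beforehand

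*Protocol article*

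**What the plan says.** The rule stands in the Statistical analyses section of the protocol article: "For all analyses, variables will be checked for confounding and/or effect-modification and will be adjusted for accordingly". It is worded for every analysis and so includes the primary one. The Compliance section identifies that outcome ("Compliance (primary outcome) measurements will commence after randomisation"), and Statistical analyses gives its model: "Compliance rates between groups will be compared by means of a multivariate linear regression analysis using compliance as a continuous dependent variable".

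The pool of candidates is wide. The Baseline measurement section lists "demographic variables, physical characteristics, sports & injury history, use of preventive measures, knowledge on injury prevention, severity of the current ankle sprain", plus treatment and rehabilitation. The rule does not confine itself to baseline. The Compliance section also collects, weekly after randomisation, how clear the instructions were and how difficult the exercises were.

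Athletes are individually randomised. The Randomisation procedure section names initial treatment, medical or non-medical, as the stratification factor; the Methods/Design part of the abstract names the medical caregiver instead. No section says that the overall arm effect remains the primary result whatever the check for effect-modification shows.

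**The concern.** Checking for confounding is a habit from observational work. Between randomised arms there is no systematic baseline confounding to find, only chance imbalance. Covariates belong in the model because they predict the outcome, and that can be decided before any outcome is seen. Under the stated rule, the covariates in the primary model depend on what the check shows.

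Effect-modification can only be checked with outcomes in hand. Adjusting for it means fitting an interaction, after which the single arm effect is no longer one coefficient of the model. Several candidate primary p-values then exist, and the rule leaves the choice among them to the data.

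Because the rule speaks of variables in general, it would also allow adjustment for clarity and difficulty ratings given after randomisation. These may lie on the path from App or booklet to compliance. The Discussion expects positive results to influence guidelines, so the primary result should rest on one model settled in advance.

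**Working it through.** **1. What a change-in-estimate check selects.** In least squares with arm and one covariate Z, unadjusted minus adjusted arm effect = g × (mean of Z in the App arm − mean of Z in the booklet arm), where g is the coefficient of Z in the adjusted model. A covariate moves the estimate only if it is both prognostic (g not zero) and imbalanced by chance. The precision gain, however, comes from g alone. The check therefore tends to drop prognostic covariates that happen to be balanced, and this is where power is lost against a fixed model.

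**2. The plan's own figure.** Sample size section: 25% against 50% full compliance, alpha 0.05, power 0.90 (printed as beta), total 158. Two-sided with pooled variance:

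n per arm = [1.96 × √(2 × 0.375 × 0.625) + 1.2816 × √(0.25 × 0.75 + 0.5 × 0.5)]² / 0.25² = (1.342 + 0.848)² / 0.0625 ≈ 77

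That is 154 in total, within 3% of 158; power with 79 per arm is 0.908. So 158 serves as the simulated trial size.

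**3. Assumptions not in the document.** Independent baseline covariates (5, 8 or 10), jointly explaining R² of the outcome; a 10% change-in-estimate criterion; interactions screened at 0.05; in the main set, an arm effect of 0.52 residual SD. The document gives no effect on the continuous compliance scale.

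**4. Type I error (%), 158 athletes, 2,500 null trials per row.** Monte Carlo SE = √(0.05 × 0.95 / 2500) = 0.4 points.

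| Covariates, R² | Prespecified | 10% change-in-estimate | Free choice | Interaction screen |
|---|---|---|---|---|
| 5, 0 | 5.1 | 5.1 | 6.6 | 19.1 |
| 5, 0.1 | 5.2 | 4.8 | 9.1 | 18.5 |
| 5, 0.3 | 5.2 | 4.1 | 14.6 | 19.9 |
| 10, 0 | 6.0 | 6.1 | 9.6 | 31.2 |
| 10, 0.1 | 5.1 | 5.7 | 12.4 | 30.4 |
| 10, 0.3 | 5.5 | 4.7 | 22.5 | 31.0 |

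Free choice means adding covariates for as long as the arm p-value falls. Interaction screen means counting an overall p < 0.05 or, after a positive interaction, a stratum-specific one. The 6.1% is mostly simulation noise: the unadjusted test gave 5.8% in the same row.

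The chance of at least one false interaction is 1 − 0.95⁵ = 0.226 for 5 independent tests and 1 − 0.95¹⁰ = 0.401 for 10; the simulated values were 0.22 to 0.23 and 0.39 to 0.41.

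**5. Power (%), 10 covariates, 1,500 trials per row.**

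| R² | Unadjusted | 10% change-in-estimate | Prespecified |
|---|---|---|---|
| 0 | 89.9 | 89.9 | 88.1 |
| 0.1 | 87.8 | 88.0 | 88.1 |
| 0.3 | 77.9 | 84.5 | 89.9 |

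A check on the last row: at R² 0.3 the standard error should shrink by √(1 − 0.3) = 0.837. The price of 10 covariates, read off at R² 0, is 0.1643 / 0.1589 = 1.034. The product is 0.865; the simulated ratio is 0.1640 / 0.1897 = 0.865.

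**6. A second set**, with 8 covariates and R² 0.3 (3,000 null and 1,500 alternative trials), agrees. Type I error was 4.9% unadjusted, 4.2% change-in-estimate and 5.2% prespecified. Choosing the best of the unadjusted, single-covariate and full models gave 10.6% (12.5% at R² 0.4). Power was 74.5%, 81.2% and 84.8% for unadjusted, change-in-estimate and prespecified. The effect size behind this set is not stated, so only the contrasts within it are used.

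**The case against.** The best defence is that the rule, applied mechanically, does little harm. It held type I error at 4% to 6%, and at R² 0.3 it gained power over an unadjusted test (81.2% against 74.5%; 84.5% against 77.9%). With covariates of no prognostic value it even beat the 10-covariate fixed model (89.9% against 88.1%). That stands, so a reader should not infer that the rule costs power in every case.

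Other stronger readings are tempting, and the document does not support them:

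- **That the plan as written inflates type I error.** The inflated figures describe an analyst who picks a favourable model, or who tests strata after a positive screen. The sentence announces neither. It also states no criterion that would exclude them.
- **That a chance interaction would displace the intention-to-treat answer.** The section promises intention-to-treat for all analyses, comparisons within baseline strata still follow allocation, and nothing says that the overall effect is dropped. What remains is that nothing keeps it primary either.
- **That the rule cannot be applied to the Mann–Whitney comparison.** Stratified rank tests such as van Elteren's exist.
- **That checking for confounding is misplaced everywhere.** Absence from sports is recorded for recurrences, and costs are also compared among injured athletes. These groups form after randomisation, and randomisation does not balance them.
- **That the missing covariate list is itself a fault.** An article may leave it to the analysis plan.

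What survives is narrower. The article does not merely omit the list. It states a data-driven way of arriving at it, and a plan that fixed the covariates beforehand would have to override that sentence.

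**Conclusion.** The point holds for the comparisons of all randomised athletes, namely compliance and the Cox model for recurrence. The stated rule makes model and estimate depend on the data where randomisation makes this unnecessary.

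Under a mechanical rule the cost is some 4 to 5 points of power against a prespecified model if covariates are strongly prognostic (84.8 − 81.2 = 3.6; 89.9 − 84.5 = 5.4), and nothing at R² of 0.1 or below. Under discretionary use, or if interaction screening leads to stratum-specific tests, type I error could be roughly 7% to 31%. Each figure rests on an assumed number and strength of covariates, so the ranges illustrate and are not bounds. The direction is firm and the size is not. The defect can be corrected before analysis and does not affect the design.

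**What to change.** For compliance and the Cox model, replace the sentence by a fixed specification:

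- Model terms: arm, the stratification factor, and a short list of baseline covariates named before analysis, for example age, sex, severity of the current sprain and previous sprain history. All fall within what the baseline questionnaire covers.
- Use the same set in both models whatever imbalance is observed, and exclude every variable measured after randomisation.
- Report interaction tests separately, as exploratory; they never replace the overall arm effect.
- First reconcile the abstract (medical caregiver) with the Randomisation procedure section (initial treatment), so that the factor entered is the one used.
- Treat the analyses restricted to re-injured athletes separately, as comparisons of subsets formed after randomisation.

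The cost is a few sentences, no new data and a few degrees of freedom. Even 10 covariates of no value raised the standard error by only 3.4% in the simulation (0.1643 / 0.1589 = 1.034), and a shorter list would cost less.

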### Objectives

The objective of this randomised controlled trial is to evaluate the implementation value of the ‘Strengthen your ankle’ App as compared to the usual common practice of providing injured athletes with written materials.

Our hypothesis is that the use of the ‘Strengthen your ankle’ App will increase compliance to the prescribed neuromuscular training program and, consequently, will decrease ankle sprain recurrence incidence.

Specific research questions that will be answered are:

• What is the compliance to the prescribed 8-week exercise program via the App and via written material?

• Is there a difference in program compliance rates between the ‘Strengthen your ankle’ App and written materials?

• Is there a difference in ankle sprain recurrence incidence rates during a 12-month follow-up, between groups applying the ‘Strengthen your ankle’ App and written materials?

• Is there a difference in direct and indirect costs during a 12-month follow-up, between groups applying the ‘Strengthen your ankle’ App and written materials?

• Is there a difference in ankle sprain residual complaints (i.e. instability, feeling of giving way, pain, and continued sports participation) after a 12-month follow-up, between groups applying the ‘Strengthen your ankle’ App and written materials?

• What is the participants’ user experience of the ‘Strengthen your ankle’ App and the written materials?

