### Follow-up measurement

After the 8-week training program, athletes will receive an online follow-up questionnaire to measure residual complaints of the initial ankle sprain and attitude towards the prescribed exercises. Both pain and feeling of giving way will be scored on five-point Likert scale for a series of questions.

Recurrent injury incidence and cost of injury outcomes will be measured once a month for a total period of 12 months. The follow-up measurements will gather information for each athlete on ankle sprains sustained during the preceding month, including details and mechanisms of this sprain and absence from sports due to the ankle sprain recurrence as a measure of recurrence severity. Finally, these online follow-up questionnaires will measure residual complaints of the initial ankle sprain. Both pain and feeling of giving way will be scored on five-point Likert scale for a series of questions, e.g. do you feel pain when being active, do you feel pain when getting out of bed in the morning, do you feel your ankle giving way when walking across the street, etc. At the last follow-up measurement (12 months) residual complaints of the initial ankle sprain will be measured again in all athletes.

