### Cost diary

In order to evaluate the cost-effectiveness of the allocated interventions, athletes who sustain an ankle sprain recurrence will be contacted by phone to obtain information on costs associated with treatment. Based on this information direct and indirect costs resulting from the sustained ankle sprain recurrence will be calculated for use in an economic evaluation. The economic evaluation will be performed from a societal perspective.

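### The between-group cost comparison in the injured population conditions on recurrence, an outcome the App is meant to reduce; absence from sports has the same problem if only athletes with a recurrence are tested

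*Protocol article*

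**What the plan says.** All references are to the protocol article.

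- **Analysis principle** (Statistical analyses): "All analyses will be carried out according to the intention-to-treat principle".
- **Costs** (Statistical analyses): mean direct, indirect and total costs are compared between the groups "both for the costs per athlete in the injured population and for the costs per athlete in the total population". The differences in means get 95% bias-corrected and accelerated bootstrap intervals.
- **Source of cost data** (Cost diary): "athletes who sustain an ankle sprain recurrence will be contacted by phone to obtain information on costs associated with treatment".
- **Cost-effectiveness ratio** (Statistical analyses): "Differences in costs and differences in ankle sprain recurrences will be included in a cost-effectiveness ratio". The sentence names no population.
- **Absence from sports** (Follow-up measurement): the monthly questionnaires record "absence from sports due to the ankle sprain recurrence as a measure of recurrence severity". The analysis is: "Absence from sports will be compared between the two groups using a Mann–Whitney test". No analysis population is named.
- **Hypothesis** (Objectives): the App raises compliance and, "consequently, will decrease ankle sprain recurrence incidence".

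**The concern.** Randomisation makes the two arms comparable as randomised. It does not make the athletes who later re-sprain in one arm comparable with those who later re-sprain in the other, because the intervention may change who belongs to that subset. A difference in mean cost among the injured mixes two things: any effect on how costly a recurrence is, and a change in which recurrences still occur.

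If the App prevents mainly mild recurrences, those that remain are on average longer and dearer, and the App looks worse per injured athlete while costing less overall. If it prevents mild and severe recurrences equally, the injured-only contrast shows nothing although total burden has fallen. An interval for this contrast would be printed beside the valid one and could be read as a treatment effect on cost. A Mann-Whitney test of absence restricted to athletes with a recurrence would have the same weakness.

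**Working it through.** **1. Who is in the injured population?** Participants requires an ankle sprain within the past two months, so every entrant is injured at baseline. A subset distinct from the total must be defined by something later. Under Cost diary, only a recurrence triggers collection of cost data. Athletes with a recurrence is the natural reading.

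**2. Is membership affected by treatment?** By the hypothesis in Objectives, yes. The contrast drops every randomised athlete without a recurrence, which does not fit intention to treat for all analyses.

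**3. Who enters the absence test?** Follow-up measurement calls absence a measure of recurrence severity, and severity has no value without a recurrence. That favours an injured-only test. Statistical analyses names only the two groups, under the intention-to-treat sentence, which permits all athletes with zero days for those without a recurrence. The text does not settle it.

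**4. Size for costs.** The plan gives no cost figure by group to reproduce. Its one anchor is the mean of about €360 per sprain in Background. Assumptions, not from the documents: 30 recurrences per 100 booklet athletes, 60% mild at €100 and 40% severe at €750; intervention costs left out.

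- Cost per injured athlete = (mild × 100 + severe × 750) / (mild + severe)
- Cost per randomised athlete = (mild × 100 + severe × 750) / 100

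Booklet arm: 18 mild and 12 severe. Sum = 1,800 + 9,000 = €10,800, which is €360 per injured athlete (matching the anchor) and €108 per randomised athlete.

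| App prevents (mild / severe) | Mild, severe left | Sum | Per injured | Per randomised |
|---|---|---|---|---|
| 50% / 0% | 9, 12 | €9,900 | €471 | €99 |
| 50% / 20% | 9, 9.6 | €8,100 | €435 | €81 |
| 50% / 50% | 9, 6 | €5,400 | €360 | €54 |
| 20% / 50% | 14.4, 6 | €5,940 | €291 | €59 |

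Cost per randomised athlete falls in every row. Cost per injured athlete rises, stays level or falls, depending only on which recurrences are prevented. The per-injured values are the same for recurrence rates of 20% to 40%, since the rate cancels.

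**5. Size for absence, if the test is injured-only.** Simulation of 2,000 trials per setting with the same recurrence rate and mix; mild absence lognormal with median 7 days, severe with median 28 days, log-scale SD 0.6 (all assumed). Group sizes follow the Sample size section: 158/2 = 79; 190/2 = 95 if 190 is a total; and 190 per group as written.

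| Prevented (mild / severe) | Per group | Mean absence among injured higher with App | Mean absence over all randomised lower with App |
|---|---|---|---|
| 50% / 20% | 79 | 65% | 78% |
| 50% / 20% | 95 | 67% | 80% |
| 50% / 20% | 190 | 74% | 89% |
| 50% / 50% | 79 | 47% | 93% |
| 50% / 50% | 95 | 49% | 95% |
| 50% / 50% | 190 | 50% | 98% |

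In the 50% / 20% setting the injured-only Mann-Whitney test was significant against the App in 8%, 9% and 13% of trials at the three sizes. With equal prevention the injured-only comparison has no direction and misses the benefit.

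**The case against.** **The valid cost analysis is already planned.** This stands. The sentence that introduces the injured population also plans the comparison in the total population, with its own interval. A reader might infer that costs are compared only among the injured, or that the cost-effectiveness ratio rests on that subset. The documents support neither.

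**The restriction for absence is an inference.** This also stands. An athlete without a recurrence has zero days of absence due to recurrence, and a rank test accepts zeros. A reader might take it as fact that absence is tested only in athletes with a recurrence. The severity wording makes that the likelier reading, but the plan does not say it.

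**The harm depends on assumptions.** Agreed. A more dramatic result is easy to produce: with 25% recurrence, lognormal absence with median 14 days, 79 per group, and an App that removes exactly the mildest third of recurrences, the App's injured-only median is higher in 88% of trials and the test is significant in 34%. That is an extreme case with no support in the documents. If a third is prevented regardless of severity, significance drops to about 4%, close to the nominal level. With a moderate tilt (45% prevented below 14 days, 22% above) it is about 6%. So the contrast could mislead; it cannot be said that it would.

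**A bootstrapped mean of days is not clearly better than a rank test.** Also fair. In the extreme case the mean per randomised athlete favours the booklet in 44% of trials. The choice of test is secondary to the choice of population.

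What the objection does not remove is that the article fixes an inferential between-group comparison in a subset defined by an outcome. That is a stated analysis choice, not a detail left to a later document.

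**Conclusion.** The point holds for costs. The injured-population contrast conditions on a post-randomisation event that the App is expected to change, conflicts with the stated intention-to-treat rule, and can miss or reverse a benefit. It rests on reading the injured population as athletes with a recurrence, which the eligibility rule and the Cost diary section make the natural reading. For absence from sports the point is conditional on an injured-only test.

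The direction and size of any distortion are unknown because the documents give no severity mix. In the illustrations the injured-only cost moves from €360 to between €291 and €471, while cost per randomised athlete falls from €108 in every case. The total-population cost comparison is sound. Neither outcome is primary, and the compliance analysis is untouched. The change is worth making but does not threaten the trial's main conclusion.

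**What to change.** - **Costs:** make the total-population comparison the only between-group inference, and state that the cost-effectiveness ratio uses the same population.
- **Absence from sports:** state that all randomised athletes enter, with zero days for those without a recurrence. The Mann-Whitney test can stay. If an adjusted estimate is wanted, a bootstrapped mean difference is an option, since the standard Mann-Whitney test takes no covariates.
- **Per-recurrence figures:** report cost and absence per recurrence descriptively by arm, without tests or between-group intervals, and note that these subsets are not randomised comparisons.

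This costs a few sentences of wording and, if the optional mean difference is used, one more bootstrap run. It uses data already planned for collection. The drawback is less sensitivity to an effect on severity alone, because the many zeros dilute it.

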## Background

Ankle sprains are the most common sports and physical activity (PA) related injury [1-3]. It has been estimated that approximately 25% of all injuries across all sports are ankle injuries. Of all ankle injuries 85% involve the lateral ankle ligaments, i.e. acute lateral ankle sprains [3]. In the Netherlands, the most recent count of sports injuries showed that there is an estimated absolute number of 3.7 M acute sports injuries each year in a sporting population of 11 M athletes [4]. Of all annual sports injuries, approximately 530,000 are ankle sprains, of which almost 40 per cent requires (para) medical treatment [5]. Our research group has previously shown in a cost-effectiveness study [6] that, disregarding the requirement of medical treatment, the mean total (direct and indirect) cost of one ankle sprain is approximately €360. This would give a rough estimate of the annual sports-related ankle sprain costs in the Netherlands of €190,800,000. In addition, there is extensive evidence that there is an up to twofold-increased risk for ankle re-injury during the first year post-injury [6,7]. In fifty percent of all cases recurrences may result in disability and can lead to chronic pain or instability, requiring prolonged medical care [8]. As such, ankle sprains continue to pose a significant burden to the individual athlete, as well as to society as a whole.

Research has shown that both externally applied supports (i.e. taping or bracing of the ankle), as well as neuromuscular training programs are very successful in preventing recurrent ankle sprains, both from effectiveness, as a cost-effectiveness perspective [3,9-11]. While such measures have not been clearly linked to a primary preventive effect, the increased risk of recurrent injury can be reduced to the same level as previously uninjured athletes.

Therefore, in all current ruling treatment guidelines secondary preventive measures - preferably through continued neuromuscular training - are recommended after rehabilitation. These secondary preventive efforts regarding ankle sprains have been associated with high short-term returns on investment. The neuromuscular program that will be the centre of the proposed project has been linked to a €100 net return for each intervention package distributed [10].

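### The bias-corrected bootstrap interval planned for the cost-effectiveness ratio can cover well below 95% when the recurrence difference is small, as the trial's own hypothesis implies

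*Protocol article*

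**What the plan says.** Statistical analyses defines the estimand of the economic evaluation: "Differences in costs and differences in ankle sprain recurrences will be included in a cost-effectiveness ratio", read as the incremental cost of preventing one recurrence. The interval rule follows: "Confidence intervals for the cost-effectiveness ratio will be calculated with bootstrapping, using the bias-corrected percentile method with 5000 replications". Nothing is said about a recurrence difference close to zero.

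The same paragraph plans two displays that do not need an interval for the ratio: "Uncertainty of this ratio will be evaluated by presenting a cost-effectiveness plane" and "An acceptability curve will also be presented". Sensitivity analyses are also planned. The Abstract names cost-effectiveness as a secondary outcome.

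The sample size rests on full compliance, which with written materials "are expected to be around 25"%, against 50% as the relevant value for the App. No recurrence rate, recurrence difference or cost difference between arms is given.

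**The concern.** A ratio is badly behaved when its denominator is not clearly away from zero. Here the denominator is the recurrence difference between two ways of delivering one program, in a trial not sized to detect it. If bootstrap replicates of that difference fall on both sides of zero, two separate problems arise.

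- **Coverage.** The bias correction uses the share of replicate ratios below the point estimate. A replicate whose denominator changes sign jumps to the far side of the ordering, so this share no longer measures bias. The limits are moved to the wrong percentiles.
- **Meaning.** A ratio from the cheaper-and-better quadrant of the plane has the same sign as one from the dearer-and-worse quadrant. Ordered together, they do not run from favourable to unfavourable.

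At stake are the error bars on the cost of preventing one recurrence, which would be published as a 95% confidence interval.

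**Working it through.** **1. The plan's own figure.** Inputs from Sample size: 25% vs 50%, "Based upon a beta of 0.90 and an alpha of 0.05", with 0.90 read as power and alpha as two-sided. The mean proportion is 0.375.

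n per arm = 2 × 0.375 × 0.625 × (1.960 + 1.282)² / 0.25² = 0.46875 × 10.51 / 0.0625 = 78.8, so 79 per arm and 158 in total. This reproduces the stated figure.

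For dropout, 158 × 1.2 = 190 is a total (95 per arm), but the text says 190 per group. That is a separate matter; 79, 95 and 190 per arm were all examined.

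**2. Recurrence contrast implied by the hypothesis.** The Background says that "there is an up to twofold-increased risk for ankle re-injury during the first year post-injury" and that "the increased risk of recurrent injury can be reduced to the same level as previously uninjured athletes". It also credits the preventive effect to compliant athletes. Assume risk r in full compliers and 2r in everyone else:

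- Booklet: 0.75 × 2r + 0.25 × r = 1.75r
- App: 0.50 × 2r + 0.50 × r = 1.50r
- Risk ratio: 1.50 / 1.75 = 0.86

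The value of r is not in the article. With r = 12.5% (assumed) the risks are 21.9% and 18.75%, a difference of 3.1 points.

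**3. How often the difference straddles zero.** SE = √[(0.219 × 0.781 + 0.1875 × 0.8125)/n] = √(0.323/n).

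| n per arm | SE (points) | difference/SE | wrong sign | 95% interval includes zero |
|---|---|---|---|---|
| 79 | 6.4 | 0.49 | 31% | 92% |
| 190 | 4.1 | 0.76 | 22% | 88% |

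The wrong-sign share is Φ(−d) and the last column is Φ(1.96 − d) − Φ(−1.96 − d), where d = difference/SE. Bootstrap simulation of this scenario gave 87–94%. Power to show a recurrence difference is 6–12% at 79, 6–14% at 95 and 8–24% at 190 per arm, for 2r from 15% to 50%.

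**4. What the bias correction does.** The limits sit at percentiles Φ(2z₀ ± 1.96), where z₀ = Φ⁻¹(share of replicates below the estimate). As an illustration, hold the cost difference at a fixed positive amount and let the estimated effect be 0.5 SE. Replicates with a larger denominator (50%) give smaller ratios. Those with a negative denominator, Φ(−0.5) = 31%, give negative ratios. So 81% lie below the estimate and z₀ = 0.87. The lower limit is Φ(1.745 − 1.96), the 41st percentile, and the upper is Φ(1.745 + 1.96), the 99.99th. The correction has discarded two fifths of the replicates from one side.

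**5. Simulated coverage of the true ratio (nominal 95%).** Assumptions: 800 trials per setting with 1000 replicates each; gamma costs with mean €360 per recurrence (Background) and coefficient of variation 1.5; App-minus-booklet cost of −€20, +€5 or +€20 per athlete. Monte Carlo error is about 1 to 4 points.

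| Risks, booklet vs App | 79 per arm | 95 per arm | 190 per arm |
|---|---|---|---|
| 17.5% vs 15% | 65–74% | 64–72% | 69–78% |
| 26.25% vs 22.5% | 71–73% | 72–75% | 72–77% |
| 43.75% vs 37.5% | 76–79% | 79% | 84–85% |
| 30% vs 15% | 91–94% | 92–93% | 94% |

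For 30% vs 20%, coverage was 85–90% at 79–95 per arm and 93–94% at 190.

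Variations at 26.25% vs 22.5% and 95 per arm: the planned 5000 replicates gave 71%, a coefficient of variation of 3 gave 70%, and cost differences of ±€100 gave 67–68%. Separate simulations with lognormal costs at 21.9% vs 18.75% gave 62–79% over 79–190 per arm.

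**6. Alternatives in the small-effect trials.** The plain percentile interval covered 94–99%, a Fieller-type set 93–98%, and the percentile interval for incremental net benefit 92–96%.

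**The case against.** The strongest reply is that the result depends on an effect the article never states. The Background says up to twofold, and its statement about restored risk covers taping and bracing as well as training. Sample size says at least 50%, and the 0.86 assumes no benefit short of full compliance. Recurrence risk, cost spread and the cost difference between arms are all assumed. With a halving of risk the planned interval does tolerably well.

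This stands as a limit on the claim. A reader might infer that the difference will straddle zero and that the interval is invalid outright; the article supports neither. But a halving between two formats of one program goes well beyond the 0.86 that the trial's hypothesis yields, and a prespecified interval should work under the hypothesised effect.

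A reader might also blame the mixing of quadrants for the undercoverage. The evidence is against this: the plain percentile interval orders the same ratios and did not undercover. Mixing quadrants makes any ordered-ratio interval hard to interpret when zero is straddled, but that is a separate defect.

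Finally, the plane and acceptability curve already show the uncertainty, and no decision rule in the article rests on the interval. That lowers the stakes, but neither display corrects limits published as a 95% confidence interval.

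**Conclusion.** The point holds conditionally. When the recurrence difference is not clearly away from zero, the planned interval can cover the true ratio well below 95%: about 65–85% at 79 to 190 per group under a recurrence risk ratio of 0.86, and about 91–94% if risk is halved from 30% to 15%. Neither the replication count nor the reading of the sample size removes the shortfall.

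The conclusion rests on compliers having half the risk of others, on assumed recurrence risks, and on assumed cost distributions and cost differences. It should not be stretched to the primary comparison: compliance and its conclusion are unaffected.

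**What to change.** In Statistical analyses, replace the bias-corrected interval for the ratio. Suggested content:

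- Report the point-estimate ratio with the cost-effectiveness plane, giving the share of replicates in each quadrant, and keep the acceptability curve.
- Give 95% bootstrap intervals for incremental net monetary benefit, λ × (recurrences prevented) − (cost difference), at willingness-to-pay values λ that the investigators fix beforehand. The quantity involves no division. At λ = 0 it is only the cost difference with its sign reversed, and the cost difference already has a planned interval, so informative values lie above zero.
- If an interval for the ratio itself is wanted, use a Fieller-type confidence set instead.

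The cost is a change of wording, with the same bootstrap replicates and no new data. The drawbacks are that net benefit must be quoted at chosen values of λ, and that a Fieller set may be unbounded when the recurrence difference is compatible with zero.
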